## Abstract

**Background:**

Developmental Dysplasia of the Hip (DDH) is one of the most common pediatric orthopedic disorders, affecting 1–3% of all newborns. The optimal treatment of centered DDH is currently under debate. This randomized controlled trial aims to study the (cost-)effectiveness of active monitoring versus abduction treatment for infants with centered DDH.

**Methods:**

This is a multicenter, parallel-group, open-label, non-inferiority randomized controlled trial studying the (cost-)effectiveness of active monitoring versus abduction treatment for infants with centered DDH in fourteen hospitals in the Netherlands. In total, 800 infants with centered DDH (Graf IIa-/IIb/IIc), aged 10–16 weeks, will be randomly allocated to the active monitoring or abduction treatment group. Infants will be followed up until the age of 24 months. The primary outcome is the rate of normal hips, defined as an acetabular index lower than 25 degrees on an antero-posterior radiograph, at the age of 12 months. Secondary outcomes are the rate of normal hips at the age of 24 months, complications, time to hip normalization, the relation between baseline patient characteristics and the rate of normal hips, compliance, costs, cost-effectiveness, budget impact, health-related quality of life (HRQoL) of the infant, HRQoL of the parents/caregivers, and parent/caregiver satisfaction with the treatment protocol.

**Discussion:**

The outcomes of this randomized controlled trial will contribute to improving current care-as-usual for infants with centered DDH.

**Trial registration:**

Dutch Trial Register, NL9714, registered September 6, 2021. https://clinicaltrialregister.nl/en/trial/29596

## Background

Developmental Dysplasia of the Hip (DDH) is one of the most common pediatric orthopedic disorders, affecting 1–3% of all newborns [1]. DDH encompasses a wide spectrum of growth disorders of neonatal and infant hips, ranging from mild acetabular dysplasia with a well-centered femoral head to severe acetabular dysplasia with dislocation of the femoral head [1, 2]. Untreated DDH can lead to chronic pain, gait abnormalities, and early-onset hip osteoarthritis [1–3]. It is estimated that up to 26% of hip arthroplasties in patients aged 40 years or younger are performed due to untreated or insufficiently treated hip dysplasia [4].

Centered DDH refers to centered hips with acetabular dysplasia, classified as Graf type IIa-/IIb/IIc with ultrasound evaluation (Table 1) [3, 5]. The optimal treatment of centered DDH is currently under debate. Abduction treatment is the most used treatment method for children under six months of age with centered DDH worldwide [6]. However, it is approximated that 85% of immature dysplastic hips will normalize at the age of three months without treatment [7]. Also, it is estimated that more than 80% of centered DDH hips (Graf IIa- to IIc) under six months will normalize without treatment [8]. This suggests that ultrasonography screening at a young age might introduce DDH overdiagnosis and possibly unnecessary treatment of immature hips that are not truly pathological.

**Table 1 Tab1:** Ultrasonography classification of hip dysplasia by Graf [9]

Type	Alpha angle	Beta angle	Description
Ia	≥ 60	≤ 55	Normal, mature hip
Ib	≥ 60	> 55	Normal, mature hip
IIa +	50–59	> 55	Physiological immaturity, age appropriate (< 3 months old)
**IIa-**	**50–59**	** > 55**	**Maturational deficit (< 3 months old)**
**IIb**	**50–59**	** > 55**	**Delayed ossification (> 3 months old)**
**IIc**	**43–49**	** < 77**	**Critical zone**
D	43–49	> 77	Decentered
III	< 43		Decentered; perichondrium upward
IV	< 43		Decentered; perichondrium horizontal or downward

A few studies have compared active monitoring and abduction treatment for infants with centered DDH [10–15]. A recent review summarizes that there is no difference in acetabular index between active monitoring and abduction treatment for infants up to four months of age with centered DDH after three months [16]. However, the included six studies showed considerable methodological heterogeneity and two non-randomized studies were rated as serious risk of bias. A large randomized clinical trial, embedded in clinical practice, is warranted to validate the outcomes of the previous studies, and study the cost-effectiveness of active monitoring versus abduction treatment for infants with centered DDH. Therefore, the current randomized controlled trial aims to study the (cost)-effectiveness of active monitoring versus abduction treatment for infants with centered DDH.

## Methods/design

### Trial design and study setting

This is a multicenter, parallel-group, open-label, non-inferiority randomized controlled trial studying the (cost-)effectiveness of active monitoring versus abduction treatment for infants with centered DDH in fourteen hospitals in the Netherlands (Amphia Hospital, Amsterdam University Medical Center, Erasmus Medical Center, HagaZiekenhuis, Leiden University Medical Center, Maastricht University Medical Center, Máxima Medical Center, Medisch Spectrum Twente, Noordwest Ziekenhuisgroep, Onze Lieve Vrouwe Gasthuis, Reinier Haga Orthopedic Center, Sint Maartenskliniek, Spaarne Gasthuis, and University Medical Center Groningen). As part of the Dutch national DDH screening program, youth healthcare professionals will refer at-risk infants for an ultrasound evaluation at the age of three months (or sooner in case of suspected dislocation) [17]. Infants will be identified and recruited after diagnosis at outpatient clinics of the participating orthopedic departments. After diagnosis and assessment of the eligibility criteria, parents/caregivers will receive the written patient information leaflet. Parents/caregivers will return for a standard-care consultation to sign the informed consent after a reflection period of seven days. After written informed consent has been obtained, randomization and baseline measurements will be performed. Infants will be followed up until the age of 24 months.

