### Allocation and blinding

Infants will be randomly allocated to the active monitoring or abduction treatment group. Randomization will be performed by a computer-generated randomization schedule. Block randomization will be used, stratifying for Graf type IIa-/IIb/IIc and participating center. Due to the nature of this study, parents/caregivers and treating physicians cannot be blinded. However, the researchers performing the data analyses will be blinded.

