### Data collection methods

Data collection is embedded in standard-care follow-up moments according to the Dutch DDH guideline (Table 3) [17]. At the enrollment consultation, baseline patient characteristics, physical examination data, and ultrasonographic measurements will be collected by the physician or researcher. Infants and parents/caregivers will return for a consultation at the orthopedic department every six weeks (± 1 week) to collect physical examination data, ultrasonographic measurements, and data on compliance and complications, until one of the endpoints (Table 2).

Additionally, baseline cost- and HRQoL questionnaires will be sent to the parents/caregivers via email. One parent/caregiver is asked to digitally fill in the cost- and HRQoL questionnaires at baseline and after 3, 12, and 18 months. The parent/caregiver will fill in two HRQoL questionnaires, one for the infant and one for the parent/caregiver. If the parent/caregiver has not filled in the questionnaires, a digital reminder will be sent after two weeks, and the parent/caregiver will be contacted by phone after four weeks.

At the age of 12 and 24 months (± 1 month), the infants and parents/caregivers will return for a consultation at the orthopedic department to collect physical examination data, radiograph measurements, and data on complications.

All members of the TRAM-Trial team will be protocol trained for standardized evaluation of included subjects.

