#### Cost effectiveness analysis

A trial-based cost-effectiveness analysis will be performed from a societal- and healthcare perspective with a time horizon of 24 months and according to the Dutch Manual for Cost Analysis in Health Care Research [19]. Incremental cost-effectiveness ratios will be calculated as societal cost per infant QALY (societal perspective) and healthcare cost per additional infant with a normal hip (healthcare perspective). Cost-effectiveness acceptability curves will visualize the cost-effectiveness probability for a range of threshold values. Total costs will be calculated by multiplying all resource use related to hip dysplasia with the costs per unit. Resource use will be extracted from hospital electronic patient files and standardized cost-questionnaires with a recall period of three months. If available, standardized, national cost-prices will be used [19]. If not available, hospital-specific- or published unit-prices will be used. The friction cost method will be used for productivity losses by parents/caregivers. The healthcare-perspective analysis will be based on the proportion of infants with a normal hip at the age of 24 months. The societal-perspective analysis will be based on the EQ-VAS of the EQ-5D-Y, which will be administered at baseline and after 3, 12, and 18 months, and will be filled out by one parent/caregiver. The base-case cost-utility analysis is based on the societal cost per QALY of the infant, obtained from the VAS of the EQ-5D-Y. Additionally, a secondary cost-utility analysis will calculate the cost per QALY of the parent/caregiver, obtained from the EQ-5D-5L. Costs and effects occurring twelve months after study inclusion will be discounted at 4% and 1.5% respectively according to the Dutch manual [19]. Uncertainty will be addressed with standard bootstrap- and sensitivity analyses.

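### The protocol does not ensure that the baseline quality-of-life and cost questionnaires are completed before the parent knows the allocation

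*Protocol article*

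**What the plan says.** On sequence, the protocol article (Trial design and study setting) states: "After written informed consent has been obtained, randomization and baseline measurements will be performed". Under Ethics and dissemination, the parent who fills in the questionnaires gives a separate consent.

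Data collection methods handles two kinds of baseline data differently. Clinical data are taken in person: "At the enrollment consultation, baseline patient characteristics, physical examination data, and ultrasonographic measurements will be collected by the physician or researcher". The questionnaires are not: "baseline cost- and HRQoL questionnaires will be sent to the parents/caregivers via email". No send date relative to randomisation is given. For a parent who has not responded, "a digital reminder will be sent after two weeks, and the parent/caregiver will be contacted by phone after four weeks". No date is given after which an answer no longer counts as baseline.

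The respondent is a parent, and Allocation and blinding says that "parents/caregivers and treating physicians cannot be blinded".

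On use, the cost-effectiveness section bases the societal analysis on the infant's EQ-VAS, "which will be administered at baseline and after 3, 12, and 18 months". The cost questionnaire looks back three months. Statistical methods says that HRQoL will be compared with GEE, without saying how the baseline value enters the model.

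**The concern.** A baseline value is useful because allocation cannot have influenced it. Here the value is self-reported by a parent who knows the arm once it is disclosed. The written workflow lets the form be completed after that moment, and possibly after a device has been fitted. A parent who answers at the first reminder may already have attended a harness check, since Interventions advises one 1 and/or 2 weeks after the start of Pavlik treatment.

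The next questionnaire comes only at three months, so baseline is the sole early measurement of EQ-VAS, ITQOL-SF47 and EQ-5D-5L. If part of the device's burden, or of the reaction to allocation, is already in that value, then subtracting it or adjusting for it removes part of the difference the trial wants to measure. The loss would tend to hide device burden, which is a plausible advantage of active monitoring. Baseline costs could be affected in the same way, because the recall window would extend past randomisation. A pre-allocation answer that was never collected cannot be recovered at the analysis stage.

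**Working it through.** The plan states no figure to reproduce on this point. The check compares what the text fixes with what it leaves open, and then sizes the possible effect.

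**Sequence.** Consent comes first, then randomisation and baseline measurements, joined by a plain conjunction. Questionnaires should not go out before the responding parent has consented, and randomisation is placed directly after consent. Completion after allocation is therefore a likely result for at least some parents, but the text does not state it.

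**Inputs from the protocol.** Questionnaires at 0, 3, 12 and 18 months; reminder at 2 weeks and call at 4 weeks; three-month cost recall, taken as 13 weeks.

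**Assumptions, not in the protocol.** An EQ-VAS effect d = 0.05 (5 points on the 100-point scale); an adjustment slope b = 0.5; trapezoidal QALYs; email sent on the day of randomisation, so that the reminder weeks count from there. The fraction f is the part of d already present in the average between-arm baseline difference. It is unknown, so a range is shown.

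**Change score and covariate adjustment.** A change score keeps d(1−f). Adjustment with slope b keeps d(1−bf).

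| f | Change score | Adjusted, b = 0.5 | Baseline term in unadjusted QALY (0.125 × f × d) |
|---|---|---|---|
| 0 | 0.0500 | 0.0500 | 0 |
| 0.25 | 0.0375 | 0.0438 | 0.0016 |
| 0.5 | 0.0250 | 0.0375 | 0.0031 |
| 1 | 0 | 0.0250 | 0.0063 |

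**QALY weight.** With times of 0, 0.25, 1 and 1.5 years, the trapezoid weights are 0.25/2 = 0.125, 1/2 = 0.5, (1.5 − 0.25)/2 = 0.625 and (1.5 − 1)/2 = 0.25. They sum to 1.5. The baseline share is 0.125/1.5 = 8.3%.

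**Cost recall falling after randomisation.** Answered at once: 0/13 = 0%. At the reminder: 2/13 = 15%. At the call: 4/13 = 31%. Even at four weeks, 69% of the window is before randomisation.

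**After the fix.** If the forms are completed before allocation is disclosed, f = 0. Nothing is lost and none of the recall window falls after randomisation.

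**The case against.** The strongest reply is that the text does not say what a critical reader may take from it. A reader might infer that the questionnaires are emailed after randomisation and that every baseline already contains the treatment effect. Neither is supported. The sentence on sequence lists two activities that both follow consent, no send date is given, and only parents who answer after learning the arm are affected. Their share is unknown. The two- and four-week contacts are a procedure for non-responders and do not mark the usual completion time; equally, four weeks is not a stated limit.

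The analysis side is also open. GEE is named without a role for baseline, and no baseline adjustment of QALYs is specified. In an unadjusted area under the curve, an early post-allocation answer would partly record the device's burden rather than remove it, and the term is small. The loss of the whole effect is the f = 1 change-score extreme. For costs, most of the recall window stays before randomisation. Finally, an article may leave timing detail to the full protocol, and the body of Table 3 was not available for this check.

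All of this limits the size and certainty of the point. It does not remove the gap. The article itself sets out the order, the delivery by email and the reminder schedule, and none of these ensures completion before allocation is known. This is a matter of data collection, which an analysis plan cannot repair afterwards.

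**Conclusion.** The point holds as a missing safeguard and a possible bias, not a demonstrated one. As written, the protocol allows unblinded parents to report baseline HRQoL and, to a lesser degree, costs after allocation is known.

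The size depends on three unknowns: how many parents answer late, how far their answers shift, and whether baseline is subtracted, adjusted for or simply included. With b = 0.5 and f between 0.25 and 0.5, adjustment would lose 12.5% to 25% of the effect, and a change score 25% to 50%. In an unadjusted QALY the baseline term is at most 0.00625 for an assumed effect of 0.05. Between 0% and 31% of the cost recall would fall after randomisation for answers at 0 to 4 weeks.

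Only secondary and economic outcomes are touched. The primary outcome is radiographic, and the clinical baseline data are taken at the enrolment consultation. The change is worth making because it is cheap and the lost information cannot be recovered.

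**What to change.** State in the protocol that the responding parent completes the baseline HRQoL and cost questionnaires digitally at the consent visit, after signing consent and before the allocation is disclosed. Sending them during the seven-day reflection period is not a substitute, because consent is signed only after that period.

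For infants already enrolled, record the questionnaire completion date against the dates of randomisation and device start. Add a sensitivity analysis that treats baselines completed after allocation as missing. Keep those infants in the analysis: dropping them would select on behaviour after randomisation.

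The cost is a small workflow change in the database, a few minutes at the visit and a slight delay to randomisation.

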### Eligibility criteria

The TReatment with Active Monitoring (TRAM)-Trial consists of infants aged 10–16 weeks who are diagnosed with centered DDH (Graf IIa-/IIb/IIc) with ultrasound evaluation. In case of bilateral DDH, only the hip with the most severe Graf classification at baseline will be included in the analyses. Additional inclusion criteria are good comprehension of the Dutch language and the written informed consent of the parents/caregivers. Exclusion criteria are hip instability (Graf type D/III/IV DDH), age < 10 weeks or > 16 weeks, (suspicion of) syndromic disease (e.g. arthrogryposis, cerebral palsy, Down syndrome), and prematurity (defined as a gestational age < 37 weeks).

### Interventions

In the active monitoring group (± delayed treatment), infants will not wear an abduction device and will be evaluated every six weeks with ultrasound and physical examination until reaching one of the endpoints (Table 2, Fig. 1). In the abduction treatment group, infants will wear an abduction device (e.g. Pavlik harness) and will be evaluated every six weeks with ultrasound and physical examination until reaching one of the endpoints (Table 2, Fig. 1). The Pavlik harness will be applied in 90–100 degrees of flexion of both hips and maximal comfortable abduction. Standard check-up after 1 and/or 2 weeks is advised after the start of Pavlik treatment. All infants in both groups will be evaluated at the age of 12 and 24 months.

**Table 2 Tab2:** TRAM-Trial endpoints

Intervention	Endpoints	Treatment
Active monitoring	1. Hip normalization	Treatment will be discontinued as maximal results have been accomplished
	2. A total period of 18 weeks	Patients will receive treatment according to the standardized Dutch national protocol for usual care
	3. No improvement is observed on two consecutive imaging evaluations	
	4. Deterioration of the hip is observed with clinical examination or imaging. Deterioration for Graf type IIc is defined as worsening or not improving into Graf type IIb within 12 weeks	
	5. Inability to perform a reliable ultrasound evaluation because of progressive development of the ossific nucleus of the femoral head	Follow-up will be continued by obtaining radiographs
Abduction treatment	1. Hip normalization	Treatment with the dynamic abduction device will be discontinued as maximal results are accomplished
	2. No improvement is observed on two consecutive imaging evaluations	Patients will receive treatment according to the standardized Dutch national protocol for usual care
	3. Deterioration of the hip is observed with clinical examination or imaging	
	4. The infant is too strong for the dynamic abduction device	Abduction treatment will be continued using a static abduction device (e.g. CAMP device) until 1, 2 or 3 is accomplished
	5. Inability to perform a reliable ultrasound evaluation because of progressive development of the ossific nucleus of the femoral head	Follow-up will be continued by obtaining radiographs

**Fig. 1 Fig1:**
[figure not shown]
TRAM-Trial flowchart

During baseline and follow-up evaluations, physical examination consists of weight measurements, asymmetric skin fold evaluation, knee height (Galeazzi test), degrees of hip abduction in flexion, and Barlow and Ortolani tests. At the age of 12 and 24 months, physical examination consists of degrees of hip abduction and leg length evaluation. Ultrasounds will be performed every 6 weeks according to the Graf method until hip normalization or technically restricted due to the appearance of the ossific nucleus of the femoral head. For the latter case, radiographs will be obtained in further follow-up. At the age of 12 and 24 months, pelvic radiographs will be performed according to a standardized protocol. Ultrasounds and radiographs will be assessed by local pediatric radiologists at the participating centers.

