### Outcomes

#### Primary outcome

The primary outcome is the rate of normal hips, defined as an acetabular index lower than 25 degrees on an antero-posterior radiograph, at the age of 12 months.

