### Data management

A data management plan was constructed. All data will be pseudonymized prior to entry into the Castor database (Castor, Amsterdam, the Netherlands). The local principal investigators and research nurses in the participating centers have access to the local code key. Two PhD-students have access to the code key of all participating centers. Source documents will be stored locally at the participating centers. All ultrasounds and radiographs will be pseudonymized and stored at MUMC + . The local principal investigators and research nurses in the centers will have access to local source documents. The two PhD-students, monitors, and the Health and Youth Care Inspectorate will have access to all source documents. All data will be stored for 15 years.

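### The 12-month radiograph that decides the primary endpoint is read locally in an open-label trial, and no masking of those readers is stated

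*Protocol article*

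**What the plan says.** Under Trial design and study setting, the protocol article describes the trial: "This is a multicenter, parallel-group, open-label, non-inferiority randomized controlled trial". For the primary outcome, a hip counts as normal by a threshold: "defined as an acetabular index lower than 25 degrees on an antero-posterior radiograph, at the age of 12 months".

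The Interventions section, after Figure 1, says who reads the images: "Ultrasounds and radiographs will be assessed by local pediatric radiologists at the participating centers". One sentence thus gives the same group of readers both the six-weekly ultrasounds and the endpoint films.

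Allocation and blinding says that "parents/caregivers and treating physicians cannot be blinded". It then offers one safeguard: "However, the researchers performing the data analyses will be blinded". The radiologists appear on neither side of that list.

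Three other statements come close to the subject:
- Interventions: "pelvic radiographs will be performed according to a standardized protocol".
- Data collection methods: "All members of the TRAM-Trial team will be protocol trained for standardized evaluation of included subjects".
- Data management: "All ultrasounds and radiographs will be pseudonymized and stored at MUMC".

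**The concern.** The endpoint turns a hand-measured angle into a yes or no at 25 degrees. Hips close to the cut can change category on a small difference in reading. If readings depend on the arm, the error enters before the data reach the analyst, and a blinded analyst will carry it faithfully into the result.

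The arms differ visibly during treatment: an abduction device in one, none in the other. Unless readers are told otherwise, routine local reading leaves arm information within reach.

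The stakes are high in a non-inferiority comparison because the margin is only 10 points. A lean favouring active monitoring could produce a false claim of non-inferiority; a lean against it could hide a true one. The same reading also feeds the 24-month rate, the time-to-normalization analysis and the healthcare-perspective cost-effectiveness ratio.

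**Working it through.** **Step 1. Does anything in the article mask the reader?** The standardized radiograph protocol is mentioned for how films are taken. Training standardizes evaluation but does not withhold allocation. Pseudonymized storage would make masked reading possible, but the article does not say that the endpoint is read from those copies. Analyst blinding acts after measurement. None of the four masks the reader.

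**Step 2. Inputs from the article (Sample size and recruitment; Statistical methods).** Normal-hip rate 80%; margin 10 points (70% versus 80%); 95% confidence interval; 400 per group with 10% loss, so 400 × 0.9 = 360 analysed per arm. I take non-inferiority to mean that the lower 95% limit for active monitoring minus abduction lies above −10 points.

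The article gives no figure for reading error, so there is none to reproduce. As a baseline without any lean, power at a true 80% in both arms is Φ(0.10/√(0.32/360) − 1.96) = 91.8%, and false non-inferiority at a true 70% versus 80% is 2.5%.

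**Step 3. Assumptions not in the documents.** Acetabular index normally distributed; SD 3, 4 or 5 degrees; a systematic lean of s degrees on the films of one arm only.

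**Step 4. Shift in the rate.** If 80% lie below 25 degrees, the mean is 25 − 0.8416 × SD.
- Films read higher by s: observed rate = Φ(0.8416 − s/SD).
- Films read lower by s: observed rate = Φ(0.8416 + s/SD).
- True rate 70%, films read lower by s: observed rate = Φ(0.5244 + s/SD).

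Example, SD 4 and s = 1: Φ(0.8416 − 0.25) = 72.3%, a fall of 7.7 points. From a true 70%: Φ(0.5244 + 0.25) = 78.1%.

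**Step 5. Effect on the conclusion.** With p the observed active monitoring rate and 80% in the other arm, SE = √(0.16/360 + p(1−p)/360), and P(non-inferiority) = Φ((0.10 − (0.80 − p))/SE − 1.96).

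Example, SD 4, s = 1, truth 70% versus 80%: SE = 0.0303; (0.10 − 0.0193)/0.0303 − 1.96 = 0.70; Φ = 76%.

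| Lean | SD | From 80%, read higher | From 80%, read lower | True 70% reads as | False non-inferiority | Power, true 80% v 80%, active monitoring read higher |
|---|---|---|---|---|---|---|
| 0.5° | 3 | −5.0 | +4.3 | 75.5% | 43% | 36.5% |
| 0.5° | 4 | −3.7 | +3.3 | 74.2% | 27% | 53.8% |
| 0.5° | 5 | −2.9 | +2.7 | 73.4% | 19% | 63.9% |
| 1° | 3 | −10.6 | +8.0 | 80.4% | 94% | 1.6% |
| 1° | 4 | −7.7 | +6.3 | 78.1% | 76% | 10.8% |
| 1° | 5 | −6.1 | +5.1 | 76.6% | 57% | 24.2% |

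A wider SD softens this but does not remove it: at SD 6, false non-inferiority is 14% for 0.5 degree and 43% for 1 degree.

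**Step 6. A lean shared by both arms.** If films in both arms read 1 degree lower and the truth is 70% versus 80%, the observed difference shrinks to between 7.6 points (SD 3) and 8.6 points (SD 5). False non-inferiority is then about 15% and 7% respectively. This is a separate and smaller problem.

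**The case against.** The strongest reply is that the article is silent, not wrong. It does not list the radiologists among those who cannot be blinded, it does not describe what they see, and reading instructions may stand in a fuller protocol. This limits the wording: what can be said is that masking is not stated. It does not remove the point. The article has a section on blinding, lists who is and is not blinded, and names elsewhere who reads the films, so the safeguard it fixes is placed on the wrong people.

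A second reply is that every size above rests on an assumed SD and an assumed lean. That stands. It also stands that the largest figures need a systematic 1-degree lean on all films in one arm.

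Four stronger readings are tempting and are not supported:
- *That the readers know the allocation, or see the referral and record.* Nothing in the document says so; it is inference.
- *That a small lean uses up most of the margin.* At 0.5 degree it takes about a quarter to a half. Only a lean near 1 degree takes more.
- *That masking would also cure a lean towards normal in both arms.* Such a lean does not depend on knowing the arm, so masking leaves it in place.
- *That the damage could never be repaired.* The radiographs are stored, and a masked re-read remains possible.

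**Conclusion.** The point holds in this form: in an open-label trial, the reading that creates the primary endpoint is assigned to local radiologists, no masking of those readers is stated, and the one safeguard given, blinded analysis, does not act on measurement.

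The exposure could matter for the conclusion. Under the stated assumptions, half a degree of arm-dependent lean is enough to lift the false non-inferiority rate several-fold above 2.5%, or to cut power well below 91.8%. These figures show sensitivity. They do not estimate a bias that is known to exist, and its direction cannot be told from the document. The change is worth making before endpoint films are read, because it is easy to prespecify.

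**What to change.** State in Interventions and in Allocation and blinding that the 12- and 24-month acetabular index used for the endpoint is measured by the same local pediatric radiologists, masked to allocation. Specifically:
- the measurement is made on the pseudonymized radiograph;
- the research request carries no arm, device or treatment information;
- the reader does not open the earlier file for this measurement;
- the value is recorded before the consultation note is written.

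This needs no new reader, visit, film or increase in sample size. It does cost a little: where the clinical report needs the earlier imaging, the endpoint measurement becomes a separate step. Masking may also fail in a few infants, for example where a device is still in use. If local masking proves unreliable, a masked re-read of the stored images is the natural fallback.
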